### Study design

This is an outcome assessor- and data analyst-blinded, randomized controlled study. The study is planned to be conducted from 1 January 2015 to 31 December 2016 in Longhua Hospital affiliated with the Shanghai University of Traditional Chinese Medicine. Stroke patients with motor dysfunction meeting the inclusion criteria will be allocated by a 1:1 ratio into either an acupuncture treatment group or a control group. Stroke patients in the control group will receive conventional rehabilitation treatment, whereas a combination of Jao’s scalp acupuncture and conventional rehabilitation treatment will be applied to the acupuncture group. The Fugl-Meyer Assessment (FMA) scale will be assessed as the primary outcome measure. The Modified Barthel Index (MBI), the Stroke-Specific Quality of Life (SS-QOL), and the Stroke Syndrome of Traditional Chinese Medicine (SSTCM) scales will be selected as secondary outcome measurements. All assessments will be conducted at baseline, week 4 (treatment 20), week 8 (treatment 40), week 12 (follow-up), and week 16 (follow-up). Figure 1 summarizes the flow of the entire trial. Figure 2 shows the study timeline, according to the Standard Protocol Items: Recommendations for Interventional Trials (SPIRIT) diagram. Additional file 1 presents the SPIRIT checklist.

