### Inclusion criteria

Participants meeting the following inclusion criteria will be included: (1) Stroke patients between 40 and 70 years old; (2) stroke was diagnosed according to the criteria of cerebral arterial thrombosis in western medicine, and apoplexy in Chinese medicine; (3) ischemic stroke confirmed by a brain computed tomography (CT) or magnetic resonance imaging (MRI) scan, where patient has a stable medical condition and clear awareness; (4) patient experienced a recent stroke, between 1 month to 6 months after onset; (5) stroke with limb motor dysfunction; (6) sufficient cognition to follow commands and Mini-Mental State Examination (MMSE) score >24; (7) voluntary participation and informed consent signed.

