### Sample size calculation

The sample size was determined using the results of our previous clinical trial and pilot trial [45–47]. The primary efficacy parameter is the change in FMA scores from baseline to the end of treatment after 8 weeks. According to our preliminary test and previous study, the primary efficacy parameter (FMA score) of the control group (rehabilitation treatment) would be increased by 9.86, and that of the treatment group (scalp acupuncture combination rehabilitation treatment) would be increased by 19.12. The FMA average standard deviation would be approximately 7.64. A two-sided 5% significance level and 90% power were considered, and the above relevant data (9.86, 19.12, 7.64, α = 0.05, 1 – β = 0.9) were input into NCSS-PASS V11.0.7 software (https://www.ncss.com/software/pass/) [48]. On the basis of the software calculation, approximately 45 participants are required in each group in order to have a sufficient sample size. With an estimated dropout rate of 20%, each group is required to have 54 initial participants.

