### Participant recruitment

Participants will be recruited from two hospitals (Longhua Hospital affiliated with the Shanghai University of Traditional Chinese Medicine and the Shanghai Changning District Tianshan Traditional Chinese Medicine Hospital, which is a Longhua Hospital branch) in Shanghai, China. Our study will be propagated via the Internet, local health-related newspapers, and posters in communities and hospitals. Prospective participants will be asked to talk face to face with study coordinators to discuss the study and provide information regarding eligibility criteria. If patients are eligible and interested in participating, they will be invited for a series of rehabilitation assessments after diagnosis by neurologists. One hundred and eight patients will be included in the study. When their informed consent has been obtained, patients will be randomized into two groups with different treatments.

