### Statistical analysis

All data will be analyzed in the clinical research center of Longhua Hospital, affiliated with the Shanghai University of TCM by statisticians using the Statistical Product and Service Solutions (SPSS ) statistical package program (version 17.0, SPSS Inc., Chicago, IL, USA). Baseline assessments will be conducted before randomization, including gender and age of patients, disease course, hemiplegia (left or right), stroke risk factors, diseased location and size, primary outcome (FMA), and secondary outcomes (MBI, SS-QOL, and SSTCM). All patients randomized to each group are included in the analysis, and the data analysis will be conducted using two-sided significance tests at a 5% significance level. All analyses will be based on the intention-to-treat principle using the last observation carried forward rule. Missing values will be handled by the mixed model for repeated measurements. Continuous variables with normal distribution will be expressed as means with standard deviations (SDs) and compared by an independent sample Student *t* test. For abnormally distributed variables, the data will be expressed as medians with ranges, and non-parametric tests will be used. Categorical variables will be expressed as number (%) and analyzed by *χ*
^2^ test or Fisher’s exact test. Descriptive statistics will be used to detail baseline participant demographics and general status characteristics of patients, such as gender, age, disease course, hemiplegia (left or right), stroke risk factors, and diseased location and size. Repeated measures analysis of variance (ANOVA) will be used to analyze value changes of FMA, MBI, SS-QOL, and SSTCM scores across five testing time points (weeks 0, 4, 8, 12, and 16). Safety analyses will be compared with the incidence of AEs in the two groups using the *χ*
^2^ test.

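### The stated FMA analyses do not condition on baseline FMA; adjusting for it would give a modest gain in precision and remove a residual conditional bias, with power not at stake

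*Protocol article*

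**What the plan says.** The Statistical analysis section of the Protocol article names three methods that bear on FMA.

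- A general rule for continuous data: "Continuous variables with normal distribution will be expressed as means with standard deviations (SDs) and compared by an independent sample Student" *t* test. The sentence does not mention FMA.
- Repeated measures ANOVA, named for FMA, MBI, SS-QOL and SSTCM, over five times of which week 0 is one.
- A mixed model for repeated measurements, named only as the way to handle missing values.

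No covariate is given for any of them, and the section does not say which is the primary test. It does say that FMA and the secondary scales are measured before randomisation. The Sample size calculation section defines the primary parameter as the FMA gain between baseline and week 8.

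Two further predictors are on record. Time since the stroke is collected at baseline, in patients who enter "between 1 month to 6 months after onset". Recruiting hospital is known, but the sections disagree on it. Participant recruitment says "Participants will be recruited from two hospitals", and Interventions also speaks of two, while Study design has the trial "to be conducted from 1 January 2015 to 31 December 2016 in Longhua Hospital" alone.

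**The concern.** Post-stroke FMA gain usually depends on the starting score, through regression to the mean and the 100-point ceiling of the motor scale. If the groups differ at baseline by chance, the difference in gains carries part of that imbalance. Entering week 0 as one of the repeated outcomes does not correct this. With complete data, the week-8 versus week-0 group contrast in such an ANOVA is just the difference in mean change.

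At stake are interval width and the conditional accuracy of the primary estimate. Both can be improved with data the trial already holds.

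**Working it through.** **Inputs from the Sample size calculation section:** "A two-sided 5% significance level and 90% power were considered"; "control group (rehabilitation treatment) would be increased by 9.86"; "scalp acupuncture combination rehabilitation treatment) would be increased by 19.12"; "The FMA average standard deviation would be approximately 7.64". The planned difference is 19.12 − 9.86 = 9.26. Stated size: 45 evaluable and 54 enrolled per group. The MCID for the upper plus lower limb score is 6.0 (Primary outcome measurement section).

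**Assumptions, not in the document:** correlation ρ between baseline and week-8 FMA of 0.5 to 0.9; equal SD σ at both times; 7.64 taken as the SD of change, since the text does not say which SD it is.

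**The plan's own figure.** n per group = 2(1.960 + 1.282)² × (7.64/9.26)² = 14.3, so 15, or 16 with the exact *t* calculation. The stated 45 is not reproduced. That is a separate matter; here it means only that the planned size is generous for its own inputs.

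**Variance.** Per patient:
- change score: 2σ²(1 − ρ)
- ANCOVA: σ²(1 − ρ²), a large-sample result with a common slope
- ratio: (1 + ρ)/2, which does not depend on the SD

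**Interval width at 45 per group.** The SE of the change-score difference is 7.64 × √(2/45) = 1.61, so the 95% half-width is about 1.96 × 1.61 = 3.16. With ANCOVA this is multiplied by √((1 + ρ)/2).

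**Power at 45 per group, normal approximation.** The unadjusted change score has 99.99% for 9.26 and 96.1% for 6.0.

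**Chance imbalance at 54 per group.** The implied baseline SD is σ = 7.64/√(2(1 − ρ)), and the SE of the baseline difference is σ√(2/54). Given a baseline difference D, the change-score contrast is shifted by (1 − ρ)D, against the group that starts higher. Take D = 1.96 SE.

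| ρ | Variance ratio | Variance cut | ANCOVA half-width | ANCOVA power for 6.0 | D (points) | Residual shift (points) |
|---|---|---|---|---|---|---|
| 0.5 | 0.75 | 25% | 2.73 | 99.0% | 2.88 | 1.44 |
| 0.7 | 0.85 | 15% | 2.91 | 98.1% | 3.72 | 1.12 |
| 0.8 | 0.90 | 10% | 3.00 | 97.5% | 4.56 | 0.91 |
| 0.9 | 0.95 | 5% | 3.08 | 96.9% | 6.44 | 0.64 |

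The shift is 1.44/6.0 = 24% of the MCID at ρ = 0.5 and 0.64/6.0 = 11% at ρ = 0.9.

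**If 7.64 is instead the SD of the score,** the variance ratios are unchanged. D is 2.88 throughout, and the shift runs from 2.88 × 0.5 = 1.44 to 2.88 × 0.1 = 0.29 points.

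**Time since onset and hospital.** The document gives no figures from which a gain could be computed.

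**The case against.** The strongest reply has four parts.

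- **The *t*-test sentence is generic.** A reader might infer that the FMA comparison is simply an unadjusted *t* test. The document does not support that: the method named for FMA is repeated measures ANOVA. This stands, but the ANOVA does not condition on baseline either.
- **Baseline is already subtracted.** A reader might infer that baseline imbalance goes wholly uncorrected. It does not, because the primary parameter is change. Over all randomisations the unadjusted estimate is also unbiased. What remains is the conditional shift in the table, which is small against the planned 9.26.
- **Nothing decisive turns on it.** One could convert the variance ratios into extra patients, for example 108/0.75 = 144 at ρ = 0.5, and infer a shortage. There is none. Power is ample without adjustment, and at ρ = 0.9 the saving is only 5%.
- **Covariates belong in an analysis plan, which is not shown.** Covariate detail and stratification may well be there, and their absence from the article is not held against it. But the article does state its comparison methods, and a better use of the same data can be proposed for them.

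A further caution also stands: the Trial status section says the study is completed, so a change of primary model could be post hoc.

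**Conclusion.** The point holds as a modest improvement at almost no cost. None of the stated analyses conditions on baseline FMA. Under the assumed ρ of 0.5 to 0.9 and equal SDs, ANCOVA would reduce the variance of the change-score comparison by 25% to 5%. It would remove a residual shift of about 1.4 to 0.6 points at a 1.96 SE baseline imbalance, with 7.64 read as the SD of change.

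This is not a rescue of power. Nor is any benefit shown for time since onset or hospital: they are plausible predictors already recorded, and no more can be said from the document. A reader might also fear a comparison of raw week-8 scores, where the cost of ignoring baseline would be larger. The definition of the primary parameter as change does not support that reading.

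**What to change.** - Name the primary comparison as the week-8 FMA difference between groups from ANCOVA with baseline FMA as a covariate, or the week-8 contrast of an MMRM adjusted for baseline FMA. Week 0 should be a covariate, not an outcome time.
- Analyse MBI, SS-QOL and SSTCM in the same way, each with its own baseline.
- Time since onset and hospital may be added as covariates, without claiming a quantified gain.
- Because the study is completed, state when the model was fixed. If unblinded results have not been seen, amend the plan first. If they have, report the adjusted model as a labelled sensitivity analysis beside the planned one.
- Separately, reconcile Study design, which names one hospital, with Interventions and Participant recruitment, which give two.

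The cost is wording and one model per scale. No new data, visits or patients are needed.

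### The endpoint is FMA change at week 8, but the only test assigned to FMA by name is a five-visit repeated-measures ANOVA, and no test is designated as primary

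*Protocol article*

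**What the plan says.** The time point of the primary endpoint is given under Sample size calculation: "The primary efficacy parameter is the change in FMA scores from baseline to the end of treatment after 8 weeks". The trial is sized there on two mean changes, 9.86 and 19.12, with an SD of 7.64. The primary outcome section names the FMA and lists all five assessments without singling one out.

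The Statistical analysis section then gives, for efficacy:

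- For the FMA by name: "Repeated measures analysis of variance (ANOVA) will be used to analyze value changes of FMA". The same sentence applies this method to the three secondary scales and to all five visits, from week 0 to week 16. No ANOVA term (group, time, group-by-time) and no week-8 contrast is named.
- For normally distributed continuous variables in general: "compared by an independent sample Student" t test, with no outcome or visit stated.
- For other continuous variables: "For abnormally distributed variables, the data will be expressed as medians with ranges, and non-parametric tests will be used".
- For incomplete data: "Missing values will be handled by the mixed model for repeated measurements", beside a last-observation-carried-forward rule.
- For all of these: "the data analysis will be conducted using two-sided significance tests at a 5% significance level".

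None of these tests is called primary.

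**The concern.** The endpoint and the FMA-specific analysis answer different questions. The sample size section asks whether the two groups differ in mean change at week 8. A repeated-measures ANOVA over five visits offers two between-group tests, and neither asks that:

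- The group main effect compares the average over all five visits. That average includes week 0, where randomisation means there is no treatment effect, so a real week-8 effect is diluted.
- The group-by-time term asks whether the group difference varies across visits. It can be significant because of weeks 12 and 16, when the Follow-up section bars scalp acupuncture and patients attend community rehabilitation.

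The tests that could address week-8 change are listed generically and not tied to it. The document therefore does not settle which p-value answers the primary question. The Trial status section says the study is completed, so the choice could be made with the data in hand. At stake is whether a positive headline result means an effect at the end of treatment.

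**Working it through.** **The plan's own figure.** Inputs: difference 19.12 − 9.86 = 9.26, SD 7.64, two-sided 5%, 90% power, 1:1 allocation. The two-mean formula gives n = 2 × (1.960 + 1.282)² × 7.64² / 9.26² ≈ 14.3, so 15 per group (16 by the exact t calculation), not the stated 45. That is a separate matter. It matters here only because the calculation is a two-group comparison of week-8 change, and because 45 per group is used below as the evaluable number.

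**The test that matches the endpoint.** With 45 per group, SE = 7.64 × √(2/45) = 1.61.

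- At 9.26 points, 9.26/1.61 = 5.75, so power exceeds 99.9%.
- At 6 points (the MCID the article gives for UE plus LE), 6/1.61 = 3.73, so power is about 96%.

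**Assumptions for the rest.** The article gives no correlation between visits. I took 7.64 as the SD of the 8-week change, with either an equal correlation between all visits (compound symmetry, 0.5, 0.7 or 0.9) or a correlation that decays with time (AR(1), 0.90 or 0.95 between adjacent visits). Then σ² = 7.64² / [2(1 − ρ₀₈)] = 58.37 / [2(1 − ρ₀₈)], where ρ₀₈ is the correlation between weeks 0 and 8.

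**Group main effect at the planned difference.** For a true pattern of 0 / 4.63 / 9.26 / 9.26 / 9.26, the difference in five-visit means is 32.41/5 = 6.48. Its SE is √(2 × σ² × r̄ / 45), where r̄ is the mean of all entries of the 5 × 5 correlation matrix.

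| Correlation | σ² | r̄ | SE | 6.48/SE | Power |
|---|---|---|---|---|---|
| Equal, 0.5 | 58.4 | 0.60 | 1.25 | 5.19 | >99% |
| Equal, 0.7 | 97.3 | 0.76 | 1.81 | 3.58 | 94% |
| Equal, 0.9 | 291.8 | 0.92 | 3.45 | 1.88 | 46% |
| AR(1), 0.90 | 153.6 | 0.85 | 2.41 | 2.69 | 76% |
| AR(1), 0.95 | 299.3 | 0.92 | 3.50 | 1.85 | 45% |

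So where visits are highly correlated, the group effect has roughly 45–76% power, against more than 99.9% for the week-8 test.

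**Group-by-time and free choice of test, by simulation (45 per group).**

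| True difference at weeks 0/4/8/12/16 | Week-8 t test | Group-by-time |
|---|---|---|
| 0/0/0/3/6 (late effect only) | about 5% | about 97% (equal), 83–85% (AR(1)) |
| 0/3/6/6/6 | about 96% | about 97–98% (equal), about 83–85% (AR(1)) |
| 0/4.63/9.26/9.26/9.26 (planned) | >99.9% | at least 99.7% |
| none | about 5% | about 5% |

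With no effect anywhere, each test alone holds about 5%. Declaring success if any one of the week-8 t test, group effect and interaction falls below 5% gives about 12–14% false positives under every correlation tried.

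**The case against.** The strongest reply is that the right test is already in the plan. Week-8 FMA change is a continuous variable, the sample size section calls it the primary efficacy parameter, and continuous variables get a two-sample t test. On that reading the ANOVA describes the trajectory of four scales, and only a label is missing. A condensed article also commonly leaves the ANOVA term and contrast to the full plan. Part of this stands: the plan contains a test that can address the endpoint, so it would be wrong to say that it has none. But the one sentence that assigns FMA a test by name points to a different analysis. That is a mismatch between two statements in the article, not an omission.

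A reader might infer four stronger points, which the documents do not support:

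- **That the ANOVA interaction loses power.** At 6 points this appears only under decaying correlation (about 83% against 96%). It vanishes under equal correlation and at the planned 9.26 points.
- **That the plan tests four visits separately at 5%.** That would give a family-wise error of about 9–16%, but the plan states no such rule, and an omnibus interaction is a single 5% test.
- **That switching to a non-parametric test by observed distribution inflates the error.** With normal data, a rule of testing normality first gave 4.4–5.9% type I error and the power of the t test. Skewed or ceiling-limited data were not examined, so no harm is shown.
- **That the investigators would claim success on follow-up visits alone.** The late-effect pattern is constructed. It shows what the interaction can detect, not what the plan says it will conclude.

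**Conclusion.** The point holds as a mismatch between the endpoint and the named analysis, with the deciding test left open. It should be fixed. It does not make the trial unable to answer its question, because a suitable test is available in the plan once it is designated.

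Its size has three parts:

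- Free choice among the three stated routes raises the false-positive rate from 5% to about 12–14%.
- The interaction can be significant in most trials (83–97% in the pattern tried) with no week-8 effect.
- The group effect, if it were the deciding term, would have roughly 45–76% power at the planned difference unless the correlation between visits is lower.

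These figures rest on assumed correlations, assumed effect patterns, 45 per group and 7.64 as the SD of change. The magnitudes would move with other values. That neither omnibus between-group term isolates the week-8 change does not depend on them.

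**What to change.** State in the analysis section that the single primary test is the between-group difference in total motor FMA (0–100) change from baseline to week 8, two-sided at 5%, reported with its 95% CI and adjusted for baseline FMA. Estimate it either as the week-8 contrast of the mixed model the section already names, with baseline as a covariate, or by ANCOVA at week 8. Make the five-visit repeated-measures ANOVA and the comparisons at weeks 4, 12 and 16 secondary. A rank-based test of week-8 change can stay as a sensitivity analysis.

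The study is reported as completed. If results are not yet known, a dated addendum is enough. If they are, the report should give the week-8 difference as primary and label the rest secondary.

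The cost is a few sentences and slightly more analysis work, with no new data. It costs no power: on the article's own inputs the week-8 comparison has more than 99.9% power with 45 per group.

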## Discussion

Chinese scalp acupuncture is a contemporary acupuncture technique integrating traditional Chinese needling methods with western medical knowledge of representative areas of the cerebral cortex. As acupuncture was developing, various physicians began to introduce western neurophysiology into the field of acupuncture and explored correlations between the brain and human body. [name], who is the founder of Jiao’s scalp acupuncture and a neurosurgeon in Shan Xi Province, is also the recognized founder of Chinese scalp acupuncture. [name] combined the modern understanding of neurophysiology and neuroanatomy with the traditional concept of acupuncture to develop the new scalp acupuncture utilized to affect the functions of the central nervous system. Scalp acupuncture uses special techniques to harmonize and regulate the functional activities of the brain and body. Many researches on scalp acupuncture have indicated positive results in treating various disorders of the central nervous system. Stroke is one of the most common diseases for which acupuncture treatment is recommended, according to the WHO [49]. In view of the motor dysfunction that occurs post-stroke, the upper one-fifth and middle two-fifths of the motor area on the scalp were selected as the primary area for the scalp acupuncture stimulation region.

In stroke rehabilitation clinical studies, rehabilitation evaluation plays an important role. The FMA and MBI were selected as the gold standards for the evaluation of acupuncture treatment’s curative effect in almost all acupuncture treatment stroke researches, both domestically and overseas. We used the FMA scale to best observe the comprehensive motor ability of stroke patients based on the specific environments and the corresponding instructions; the FMA reflects the motor dysfunction level of stroke patients and is widely applied in the evaluation of motor dysfunction after stroke [50]. The MBI was used as an individual-level assessment scale to evaluate daily life activities of stroke patients; it responds to the complex activity ability and necessary functional skills of patients in daily environments and is often used to assess the degree of influence of motor dysfunction in families and social environments [51]. However, in Chinese medicine, stroke itself is thought to involve several interpromoting disease mechanisms, possibly including qi stagnation, heat, phlegm, blood stasis, and wind. Hence, the common name for stroke in Chinese medicine is wind stroke. According to the “four diagnostic methods” of TCM, the syndrome changes in stroke patients are in a dynamic development process. These symptoms’ academic terminologies are not relevant to the understanding of western traditional medicine for the symptoms of stroke diagnosis, including hemiplegia, aphasia, and facial nerve paralysis, etc. [52]. Many motor function assessment scales do not accurately reflect the actual curative effect of acupuncture based on syndrome differentiation of TCM in a certain stage of stroke. The study of acupuncture treatment of stroke should fully reflect and embody the characteristics of TCM [53]. It needs to develop the evaluation standard of acupuncture’s curative effect based on TCM symptomatology. It is not conducive to reasonably judge the effectiveness of acupuncture intervention based on the priority of “syndrome differentiation” because of the lack of an appropriate therapeutic effect evaluation standard of syndromes. However, SSTCM in this research conforms to the TCM identification rule of similar syndromes and highlights the advantages and characteristics of TCM [54, 55].

Acupuncture is a frequently used therapy for stroke rehabilitation in China, but the evidence of its effect from previous studies seems to be inconclusive [56]. Some systematic reviews have been done to study the effect of acupuncture on stroke rehabilitation [14, 25, 57, 58]. These reviews have drawn consistent conclusions that acupuncture appears to be safe and effective for stroke rehabilitation, but the benefits require further confirmation with larger, more transparent and well-conducted randomized clinical trials. Thus, the purpose of this research is to observe the therapeutic effect of scalp acupuncture using Jiao’s motor area for motor dysfunction in patients with ischemic stroke according to both international general evaluation scales and TCM evaluation systems.

Under strict quality control, this study could potentially confirm whether or not scalp acupuncture on a motor area is an effective adjunct to the standard rehabilitation treatment for stroke patients with motor dysfunction. This study also aims to explore the correlation between the TCM symptoms improved and the motor function recovery for patients with stroke, which is of great significance in further improving the evaluation system of acupuncture treatment on motor dysfunction in these patients.

